| Objectives, Specific Aims and Rationale *Objective*  The overarching objective of this study is to better understand the harms of preventative treatments (antihypertensives, statins and antiplatelets) by quantifying an individual’s baseline risk of harm and the modifying effect of treatment.    *Specific aims*  Aim 1: Derive prognostic models for an individual’s risk of adverse events associated with cardiovascular prevention treatment (antihypertensives, statins and antiplatelets). Adverse event outcomes will include falls (antihypertensives), myopathy (statins) and bleeding (antiplatelets).  Aim 2: Externally validate each model.  Aim 3: Use causal inference methods (propensity score matching, instrumental variable analysis) to examine whether modification of treatment could have an important impact on the risk of adverse events.  *Rationale*  The proposed work will develop and validate new prediction tools for an individual’s risk of harms from cardiovascular prevention medication. This information will be combined with existing tools for the benefits of treatment and be used to form a new strategy that better targets preventative therapy at those with the most to gain. By empowering patients and clinicians to better understand the risks of preventative medications, this work will promote a more patient-centred, shared-decision making approach to cardiovascular disease prevention in primary care. |

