| Study Type Hypothesis testing |
| Study Design Longitudinal cohort study |
| Feasibility counts There are approximately 5.5 million patients in England, aged 40+ and with up to standard registration for a period between 1/1/1998 to 31/12/2017 in the CPRD GOLD. Restricting to English practices (linked to HES and ONS) and only including patients fulfilling the eligibility criteria listed below, the expected population is approximately 3.3 million and out of these we expect 216,000 fall events, 230,000 myopathy/muscle pain events and 1,200 intracranial haemorrhage events. |
| Sample size considerations We have based our sample size calculation on the least common of the primary outcomes listed above (intracranial haemorrhage), and used the method developed by Riley *et al.,*^40^ to minimise the potential for overfitting and ensure precise estimates of key parameters. A sample size of approximately 80,000 patients is required for the development of a clinical prediction rule for this outcome, assuming an event rate of 24.6 per 100,000 person years,^41^ a median follow up of 7 years,^42^ a conservative estimate of Nagelkerke’s R^2^ statistic of 0.15 and a maximum number of 40 parameters per model.  Feasibility counts showed that this sample size is adequate for the development of the prediction rules. Since Intracranial bleeding is the rarest of the primary outcomes to be studied, the sample size will be sufficient for all other outcomes of interest. For validation, Vergouwe *et al.,*^43^ consider at least 100 events per sample population to be “substantial” and we will comfortably exceed this in our validation cohorts for each outcome of interest.  For analyses using causal inference methods (propensity score matching and instrumental variable analysis), assuming clinically significant increased rate of each adverse event with treatment of 10%, and an event rate of at least 0.5% per year in the non-exposed group, approximately 88,380 patients (44,190 in each group) and 4,634 events will be required to accurately define the relationship between preventative treatment and adverse events, with 90% power and an alpha of 0.05. |

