| Data/ Statistical Analysis **Prognostic modelling**  ***Aim 1 – prognostic model derivation (primary analysis)***  Where feasible and appropriate, flexible parametric survival models will be derived in the CPRD GOLD for each outcome separately. Baseline survival over time will be estimated using the Royston-Parmar approach of restricted cubic splines on the cumulative log hazard scale. In contrast to Cox regression, this allows a smoothed estimate of the baseline survival function to be derived, and the time period of prediction to be varied, facilitating individualised risk prediction. For the primary analysis, a 10-year period of prediction will be considered. Further sensitivity analyses will be conducted examining a 5-year period. Where insufficient data are available, or modelling procedures become prohibitively complex (computationally), simpler approaches such as Cox regression will be considered.  Each drug class (prescribed in the 12 months prior to the index date) will be entered into the model as a binary variable to allow for multiple treatments to be considered in each model. Where appropriate, models will be constructed with all other variables entered as continuous (not categorised) variables, and potential non-linear trends will be examined. Transformations or fractional polynomials will be used if non-linear trends are detected. Where hazard ratios are not proportional, interactions of effects with time will be included. Further interaction terms, identified in an accompanying systematic review, accounting for treatment effects which differ across specific populations may be included. Where appropriate, models will be reduced and candidate predictors selected for inclusion based on p values of association. Time since cohort entry will be used as the underlying time function in each survival model.  In a further analysis, we will extend the modelling process as described above to account for competing risk of death from other causes. This will produce a model that predicts the risk of adverse events from cardiovascular treatment over time, in the real world where individuals might die from other causes and thus prevent cardiovascular treatment adverse events from occurring. We will again use a flexible parametric modelling framework to estimate the sub-distribution hazard and cause-specific cumulative incidence functions.^45^  Missing data will be handled, under a missing at random assumption, using multiple imputation (see below) followed by Rubin’s rules to combine parameter estimates across studies.  Where feasible and appropriate, each model will be internally validated using the bootstrap method, to allow optimism-adjusted estimates of calibration and discrimination performance to be obtained. Adjustment for overfitting will be undertaken using a uniform shrinkage factor identified from bootstrapping, followed by re-estimation of the cumulative baseline sub-distribution hazard function (and thus baseline cumulative incidence function) to maintain overall calibration between observed and predicted risks. Given the large sample size, overfitting is likely to be small (see sample size calculation above). If bootstrapping is computationally infeasible due to the large sample size, then a smaller random sample of the population will be used or alternative internal validation methods employed such as cross validation.  ***Aim 2 – prognostic model validation***  External model validation will be undertaken using data from CPRD Aurum. The accuracy of risk predictions from each model will be assessed with calibration plots and 5 and 10 years, calibration measures (slope, E/O statistics), measures of overall fit (using pseudo-R^2^ estimates) and discrimination measures (C-statistics and D-statistics).  ***Aim 3 – causal inference analysis***  For most of the outcomes described in this proposal, the association and magnitude of effect with treatment is not well defined in randomised controlled trials. We will therefore undertake causal inference work to examine whether modification of treatment could have an important impact on the risk of adverse events using two causal inference methods: propensity score matching and instrumental variable analysis.  For the propensity score analysis, eligible patients will be matched 1:1 at the index date using propensity scores, which indicate the likelihood a patient will be prescribed treatment on the basis of their known (pre-treatment) characteristics and other known information which might influence the decision to treat. Predictors of preventative drug prescription will be explored in a logistic regression model. Matched patients will be compared using the Cox proportional hazards models, but hazard ratios will only be adjusted by factors unbalanced at baseline which are not already included in the propensity score model. Time since cohort entry will be used as the underlying time function in each model.  For the instrumental variable analysis, GP’s previous antihypertensive prescribing preferences will be used as an instrument to predict the likelihood of actual treatment. Risk of adverse events will be estimated in patients attending a GP considered a high prescriber of preventative medication and compared to those attending a GP considered a low prescriber. If the results from the propensity score matching suffer from unmeasured confounding, they will differ from those of the instrumental analysis. If this is the case, these models will be refined with additional factors to achieve better adjustment and matching. Where all approaches provide similar results, we can be more confident that the findings are accurate and reliable.^46^  A similar approach will be applied to secondary outcomes, for example, memory loss which has been hypothesised as being linked with statins^47^ and is a concern of many patients in practice, but there is no evidence to support this association from trials.^48^ We recognise that the evidence base may change for some outcomes over the next few years, and so the need to test the associations between treatment and certain outcomes may change.  *Subgroup and sensitivity analyses*  Where possible and appropriate, analyses of treatment associations will be examined in subgroups of the population. These will include age, sex, baseline blood pressure and cardiovascular risk, by drug type/dose/intensity and past medical history. Subgroup definitions will be agreed by expert opinion or taken from an accompanying systematic review of previous trials, examining the same topic.  Sensitivity analyses will be undertaken examining risk models for outcomes defined according to both hospital and primary care records. We will also explore the impact of our definition of myopathy and muscle pain, focussing on formal diagnostic codes for myopathy only. Models utilising a 5-year follow-up will be examined as a further sensitivity analysis. The primary analyses will examine the association between treatment and outcomes, assuming treatments are not altered or modified in the future. Where possible, sensitivity analyses will examine treatment entered as time varying covariates, and censor patients who have treatments removed or switched following the index date. |

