| Plans for addressing missing data There is potential for missing data in this study, particularly with variables such as ethnicity which are recorded with varying degrees of accuracy in routine practice. Because this analysis is focused on treatment for prevention of cardiovascular disease, accurate selection of the sample population is important and therefore any patients with insufficient data available to define their blood pressure or cardiovascular risk status at baseline (index date) will be excluded. Where there is no record of blood pressure lowering, statin or antiplatelet treatment, it will be assumed the patients were not exposed to blood pressure lowering, statin or antiplatelet treatment.  Patient eligibility includes only using ‘acceptable patients’ in the analysis, and therefore there is no need to impute age and sex. Where there is no record of smoking history or alcohol consumption, patients will be assumed to be non-smokers and non-drinkers. Likewise, those with no record of co-morbidities will be assumed to have no history of these conditions. All other covariates (including BMI, ethnicity and IMD) used in the prognostic or casual inference modelling will be imputed using multiple imputation. BMI and will be treated as a continuous variable.  All analyses of treatment associations with outcomes will be conducted by intention-to-treat, and patients moving practice after the index date (and therefore being lost to follow-up) will be censored at the point at which they are no longer active in the database. |

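### The primary treatment analyses are described as assuming unchanged treatment, but they estimate the effect of treatment status at index, whatever is prescribed later

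*Protocol*

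**What the plan says.** The Data/ Statistical Analysis section, under subgroup and sensitivity analyses, states: "The primary analyses will examine the association between treatment and outcomes, assuming treatments are not altered or modified in the future".

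Other places fix how the primary analyses are run:

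- Exposure in the prognostic models (same section): "Each drug class (prescribed in the 12 months prior to the index date) will be entered into the model as a binary variable".
- Exposure in the propensity analysis (same section): "eligible patients will be matched 1:1 at the index date using propensity scores".
- Unexposed patients (Plans for addressing missing data): "Where there is no record of blood pressure lowering, statin or antiplatelet treatment, it will be assumed the patients were not exposed".
- Analysis principle (same place): "All analyses of treatment associations with outcomes will be conducted by intention-to-treat". The only censoring named there is for patients who move practice.
- Horizon (Data/ Statistical Analysis): "For the primary analysis, a 10-year period of prediction will be considered".
- Exit (Definition of the Study population): end of linked data, last practice upload, transfer out, death or the outcome. Starting, stopping or switching a drug is not an exit.

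The sentence after the first quote plans sensitivity analyses, where possible, with treatment as a time-varying covariate and with censoring when treatment is removed or switched. A 5-year analysis is also planned. None of the four amendments changes these points.

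**The concern.** Intention-to-treat on index status estimates the effect of being treated or untreated at index, followed by whatever prescribing comes later. That equals the effect of unaltered treatment only if nobody changes treatment. Nothing in the primary analyses enforces that condition or corrects for its failure.

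The condition is also implausible on the protocol's own terms. Patients enter after a first systolic reading of 130 mm Hg or more, a CVD risk of 5% or more, or a first CVD event, so some who are untreated at index can be expected to start later. The protocol itself foresees removal and switching, since it plans sensitivity analyses for them.

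The consequence lies in interpretation. The stated objective is to quantify an individual's "baseline risk of harm and the modifying effect of treatment". In a study of harms, a ratio pulled towards 1 errs on the side of reassurance. A reader who takes the protocol's description at face value would read the primary ratio as the effect of staying on a drug against staying off it.

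**Working it through.** **1. The plan's own figure.** Sample size considerations gives a 10% rate increase, 0.5% per year in the unexposed, 90% power and alpha 0.05, leading to 4,634 events and 88,380 patients.

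- Events (Freedman, two-sided): (1.960 + 1.2816)² × [(1 + 1.10)/(1.10 − 1)]² = 10.507 × 441 ≈ 4,634. This matches.
- Patients: unexposed 10-year risk 10 × 0.5% = 5%; exposed 1 − 0.95^1.10 = 5.49%; mean 5.243%. Then 4,634 / 0.05243, rounded up in each group, gives 88,386 against 88,380 stated.

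The stated size is thus reproduced with about 10 years of follow-up and the full ratio of 1.10 throughout. It contains no allowance for switching.

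**2. How far index status departs from sustained treatment.** The start rate *a* and stop rate *d* are not in the document and are assumed here. The true on-treatment ratio is the plan's 1.10. The time span *T* is either 10 years (the primary horizon) or 7, from "a median follow up of 7 years", which the protocol assumes for the prediction-model sample size. Rates are constant and non-informative, and nobody switches back.

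- Share of index-untreated follow-up on drug: u = 1 − (1 − e^(−aT))/(aT)
- Share of index-treated follow-up on drug: t = (1 − e^(−dT))/(dT), or 1 if d = 0
- Ratio by index status: (1 + 0.10 t)/(1 + 0.10 u)
- Share of log ratio lost: 1 − ln(ratio)/ln(1.10)

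| Start/yr | Stop/yr | T (years) | u | t | Ratio | Log ratio lost |
|---|---|---|---|---|---|---|
| 3% | 0 | 7 | 0.098 | 1 | 1.089 | 10% |
| 5% | 0 | 7 | 0.156 | 1 | 1.083 | 16% |
| 5% | 0 | 10 | 0.213 | 1 | 1.077 | 22% |
| 10% | 0 | 7 | 0.281 | 1 | 1.070 | 29% |
| 5% | 5% | 5 | 0.115 | 0.885 | 1.076 | 23% |
| 5% | 5% | 7 | 0.156 | 0.844 | 1.068 | 31% |
| 5% | 5% | 10 | 0.213 | 0.787 | 1.056 | 43% |

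Worked line (5% start, 5% stop, 7 years): u = 1 − (1 − e^(−0.35))/0.35 = 0.156; t = 0.844; ratio = 1.0844/1.0156 = 1.068.

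**3. Check with a second model.** A two-state on/off model over 10 years lets patients move back and forth and removes those who have had the event. The index-status ratio is 1.082 at 2% per year each way, 1.062 at 5% and 1.042 at 10%. Direction and rough size agree with step 2.

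**4. Effect on the absolute risk of the index-untreated.** In the same model at a ratio of 1.10, their 10-year risk is 5.04%, 5.09% and 5.14% at 2%, 5% and 10% per year each way, against 5.00% if never treated. At the plan's effect size the shift in absolute risk is small; the relative contrast is what changes.

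**The case against.** Four points deserve weight.

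- **There is no contradiction of procedure.** Carrying index exposure forward is what intention-to-treat does, and the sentence can be read as stating that convention before turning to the time-varying analyses. This stands. The fault is in how the result is described, not in two instructions that cannot both be followed.
- **Later change is already examined.** A time-varying treatment term would capture index-untreated patients who start, and the 5-year analysis leaves less time for switching (23% of the log ratio lost against 43% at 10 years, in the 5%-each-way case). This stands in part. The analyses are conditional on feasibility, leave the primary estimate as described, name removal and switching but not starting in the censoring rule, and state no handling of informative change.
- **The size is assumed.** It is. Attenuation also needs a real effect and roughly non-informative switching. Residual confounding could move the estimate either way.
- **A full sustained-treatment model is a matter of choice.** It is a debatable trade-off, given the computational limits behind Amendment 2, and such detail is commonly left to the SAP.

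A reader might draw three stronger inferences that the protocol does not support:

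- *That it promises a never-treated risk.* It speaks of baseline risk. Amendment 1 puts existing users into Aims 1 and 2, and drug class is a predictor. Risk given status at index under usual care is a legitimate prognostic target.
- *That the decision tool will show a wrong treated-against-untreated difference.* No section says the tool's contrast is the Aim 1 coefficient. The Study Background assigns quantifying and combining benefits and harms to other projects, and the section on outcomes leaves their use in the final calculators to later work.
- *That power collapses.* A power figure at 4,634 events fits none of the primary outcomes. The expected cohort counts are 216,000 falls, 230,000 myopathy or muscle pain events and 1,200 intracranial haemorrhages.

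**Conclusion.** The point holds as one of labelling and interpretation. The primary analyses do not have the property the protocol gives them: they compare groups by treatment status at index, under whatever prescribing follows. If treatment is harmful and switching is roughly non-informative, the ratio lies nearer 1 than the effect of sustained use. For a true ratio of 1.10, an assumed 5% per year starting gives 1.083 at 7 years and 1.077 at 10. Adding 5% per year stopping gives 1.068 and 1.056. These are illustrations, because the protocol supplies no switching rates. Intention-to-treat as the primary approach remains defensible once it is named for what it estimates.

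**What to change.** 1. In the Data/ Statistical Analysis section, replace the part of the quoted sentence after the comma with: *according to treatment status at index, regardless of later treatment changes*.
2. State there that the primary hazard ratios and predicted risks are not to be interpreted as the effect of sustained treatment against none.
3. Report, by year of follow-up, the share of index-untreated patients on treatment and of index-treated patients off it. This replaces the assumed rates above with observed ones.
4. Make the planned time-varying and censoring sensitivity analysis cover starting among the index-untreated as well as stopping among the index-treated, and report it beside the primary estimate for each primary outcome.

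The cost is an edit, one descriptive table per exposure from prescription records, and a wider scope for an analysis already planned. The sensitivity estimate will have wider intervals and may itself be biased if the reasons for changing treatment are related to the outcome, so it should be read beside the primary result and not in its place.
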